#### Qualitative instruments

The CFIR interview guides will inform the interviews tailored for each participant group.^18^

*Patient interview*. Twenty patients will be interviewed to provide further feedback about the acceptability of the intervention. Patients will be purposively sampled with self-reported low-income, and maximum variation will be considered in sex, age, and self-reported consultation experience when inviting patients for an interview. Interviews will focus on the acceptability of the intervention for patients, suggested improvements, and any unintended consequences.*Clinician interview*. At least two clinicians from each practice will be interviewed to assess how the intervention works within the consultation and any unexpected effects. Interviews will focus on the feasibility of the intervention in daily practice, suggested improvements, and sustainability of the intervention.*PHN interview*. Up to five PHN staff who have been involved in the implementation of the REACH resources will be interviewed. The research team will focus on The CFIR 'outer setting' to better understand how the broader policy environment has influenced the implementation process.

### Data analysis

Both qualitative and quantitative data will be used to assess the acceptability, feasibility, and relative effectiveness of the intervention. The data will be collected concurrently and integrated to gain a better understanding of the implementation process for REACH.

#### Quantitative analysis

Quantitative data will be analysed descriptively, with means and standard deviations or medians and ranges reported for continuous variables, and proportions for categorical variables. Correlations will be calculated using Spearman rho (ρ) owing to the anticipated non-normal distribution of scores. Repeated measures data will be analysed using a non-parametric statistics such as the McNemar and Wilcoxon signed-rank test. Multiple regressions will be conducted to assess associations between the intervention measures.

#### Interrupted time series

An interrupted time series analysis will be performed using data from the enrolled clinics, as well as the 850 clinics within the same catchment to determine how much alcohol screening has changed in the intervention clinics and across whole PHN over the study period.

Analyses will be computed in SPSS (version 24).

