**Method:**

The implementation strategies and resources will be trialled in five general practices over 12 months. The primary outcome will be change in the proportion of adult patients with a complete alcohol history in their electronic medical records. Baseline data collection includes a practice survey to describe practice routines for ABIs and de-identified patient medical record data on completed alcohol histories (repeated at 3, 6, 9, and 12-months post-intervention). Survey and interview data will also be collected from clinicians, patients, and primary health network staff to assess acceptability and feasibility of the intervention.

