### Data collection methods

Table 1 shows data collection at the patient, provider, practice, and PHN level.

**Table 1. table1:** Data Source and data collection timepoints

Data source	Practice	Provider	Patient	Primary health network
Tool or survey	*Electronic patient database (PENCS CAT4^TM^*^13^)	Practice survey	NoMAD tool^a^	Interview	Patient survey (all)	Interview	Follow-up SMS survey	Interview	Project timelines
Contact point timeline									
Baseline	X	X							
Post- consultation					SMS link	Telephone			
3 months	X						X	X	X
6 months	X		X				X	X	X
12 months	X		X	X			X		X

SMS = short message service.

a Normalisation Measure Development questionnaire.^17^

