### Quantitative instruments

*De-identified patient data from Pen CS CAT4.*^13^ The PHN receives data from all practices in the catchment relating to completion of patient alcohol histories. A data-sharing agreement will be entered into with the PHN and participating practices to access this data. The PHN will provide data on the patients with complete alcohol histories as determined by recording of 'drinker', 'non-drinker', 'nothing recorded', and 'patient <15 years of age with nothing recorded' in the patient’s electronic medical record. The baseline measure will include all active patients; that is, those with at least three visits in the past 2 years. At 3 months and 6 months, the change in proportion of patients with an alcohol history will be measured by comparing the proportion of patients with at least one visit to the practice in the preceding 3 months who had a complete alcohol history. These measures will be available for all other clinics (approximately 850) in the same catchment area for comparison.*Practice survey*. This will be administered at baseline to collect information about the practice’s structure, staffing, record management systems, patient load and demographics, and processes for patient intake and assessment relevant to ABIs.*NoMAD* (Normalisation Measure Development) *tool.^17^* The NoMAD tool is a quantitative survey to be completed by participating GPs, practice nurses, and practice administrative staff to assess how well ABIs were embedded into everyday practice.*Patient survey*. This will be via SMS to capture data on whether patients were asked about alcohol use, how they found the experience, their alcohol use (AUDIT-C),^16^ and demographics including low income status.*Patient survey for patients with risky alcohol use*. Patients who self-report risky alcohol use (AUDIT-C) in the patient survey will be invited to participate in quarterly follow-up SMS surveys. Information will be collected on:

The average weekly consumption of alcohol in standard drinks.The frequency of episodes of high-risk drinking.The number of attendances at the general practice.

A subgroup analysis based on self-reported low-income status will be completed.

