#### Qualitative analysis

Audio files of interviews will be de-identified and professionally transcribed. Analyses will be conducted using NVivo (version 10 or higher).

Although the interview guides will be based on CFIR, inductive thematic coding will be used to ensure the findings are grounded in the data and not a pre-existing framework.

Summarised findings and early interpretations will be discussed with the research team in regular small team meetings. The authors will also meet on a minimum of two occasions with the entire investigator team to finalise the themes from the data.

Table 2 outlines the approach to the mixed-methods analysis of the data.

**Table 2. table2:** Mixed-methods data collection, analysis, and outcomes: implementation matrix adapted from Guetterman *et al*
^19^

**Data type**	**Study aim**	**Data collection procedure**	**Data analysis** **procedure**	**Theoretical framework**	**Products or outcomes**	**Points of integration**
Qualitative	To identify the barriers and facilitators to implementing alcohol BIs in general practice	Interviews: patients; clinicians; practice staff; PHN staff	Inductive thematic coding	CFIRRE-AIM	Perception of implementation processes from multiple viewpoints (acceptability; adoption; fidelity)	Triangulate with NoMAD data to inform implementation process.Compare with practice level data on % alcohol intake recording to look for patterns on increased uptake, or not
Quantitative	Increase uptake of alcohol BIs	Routine data extraction from practice to PHN (drinker, non-drinker, not recorded; sex; age); PHN to share the amalgamated data with research team	Descriptive statistics every 3 months.Interrupted time-series analysis compared with all practices in PHN catchment. Data will be collected monthly	CFIRRE-AIM	% change in patient records with alcohol intake recorded (reach; adoption)	Compare with qualitative interview data to understand barriers and facilitators to % change
Quantitative	To identify the barriers and facilitators to implementing alcohol BIs in general practice	NoMAD survey from practice managers and clinicians	Likert scale	Normalisation Process Theory	Measure of provider assessment of potential 'normalisation' of new procedure (acceptability; adoption; sustainability)	Triangulate with interview data from providers to identify implementation processes

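### The article names an interrupted time series but fixes neither its pre-launch months nor a single denominator; if the series starts at baseline, the pre-intervention trend cannot be estimated

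*Protocol article*

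**What the plan says.** **The analysis.** The Interrupted time series section states: "An interrupted time series analysis will be performed using data from the enrolled clinics, as well as the 850 clinics within the same catchment". Its purpose is "to determine how much alcohol screening has changed in the intervention clinics and across whole PHN over the study period". It gives no number of time points before or after launch.

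**The extraction schedule.**
- The abstract has a baseline extraction, "repeated at 3, 6, 9, and 12-months post-intervention".
- Table 1 (Data collection methods) marks the electronic patient database at baseline, 3, 6 and 12 months. It has no row before baseline and none at 9 months.
- Quantitative instruments describes one baseline measure and measures at 3 and 6 months.
- Table 2 (under Qualitative analysis) has quarterly descriptive statistics and then, as a separate entry, "Interrupted time-series analysis compared with all practices in PHN catchment. Data will be collected monthly". No start month is given.

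**The denominators.** Quantitative instruments defines the baseline on active patients, meaning at least three visits in 2 years. It defines the 3- and 6-month measures on patients with at least one visit in the preceding 3 months.

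**The data source.** The same section says: "The PHN receives data from all practices in the catchment relating to completion of patient alcohol histories". A data-sharing agreement is still to be made.

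**The concern.** An interrupted time series measures the effect as a departure from the level and slope that were already under way. It therefore needs several comparable observations before the intervention. Each extraction schedule that the article sets out has one such observation, and the only text that could supply more, the monthly collection in Table 2, does not say when it begins.

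This matters because the trial is single-arm and starts during a pandemic, which the Discussion accepts may alter the findings. The time series is the planned analysis best placed to separate the strategy from secular and pandemic change. If its pre-launch part is one point on a different patient base, it cannot do so, whatever its label.

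**Working it through.** The article states no power or number of points for this analysis, so there is no figure of its own to reproduce. The check is whether the model can be estimated under each schedule the article gives.

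**Model.** Y(t) = b0 + b1·t + b2·D + b3·D·(t − t0). Baseline is month 0, D = 1 after launch, and t0 = 1 is the first post-launch month. Here b1 is the pre-intervention slope, b2 the level change at t0 and b3 the slope change.

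**One pre-point.** The only row with D = 0 has t = 0, so D·t = t in every row. Hence D·(t − 1) = t − D: the fourth column is the second minus the third, and one parameter is lost.

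| Schedule | Points | Pre-points | Rank |
|---|---|---|---|
| Table 1: 0, 3, 6, 12 | 4 | 1 | 3 of 4 |
| Abstract: 0, 3, 6, 9, 12 | 5 | 1 | 3 of 4 |
| Monthly from baseline: 0 to 12 | 13 | 1 | 3 of 4 |
| Monthly, one earlier month added | 14 | 2 | 4 of 4 |
| Monthly, 12 pre-points | 24 | 12 | 4 of 4 |

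With the comparator clinics as a second series (8 parameters), a single pre-point gives rank 6 of 8. The comparators have the same gap, so they do not fill it. More post-launch months do not help either, because the missing information lies before launch.

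One qualification: if the level change is placed exactly at baseline (t0 = 0), b2 becomes formally estimable, because no slope has to be projected forward. It then rests on one observation, and b1 and b3 remain inestimable.

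**How many pre-points are useful.** The article gives no number, so this is an assumed range: p monthly pre-points, 12 monthly post-points, independent errors with residual SD 1. For p equally spaced points, S(p) = p(p² − 1)/12, so S(12) = 143. The SE of the pre-slope is 1/√S(p), and the SE of the slope change is √(1/S(p) + 1/143).

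| p | S(p) | SE pre-slope | SE slope change |
|---|---|---|---|
| 2 | 0.5 | 1.41 | 1.42 |
| 6 | 17.5 | 0.24 | 0.25 |
| 12 | 143 | 0.084 | 0.118 |
| 24 | 1150 | 0.029 | 0.089 |

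Two pre-points restore full rank in name only. Most of the gain is reached by about 12.

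**Denominator.** If the stated measures feed the series, the step at launch contains the intervention effect plus the difference in recording between the two patient groups on the same date. The article gives neither proportion, so this second part cannot be sized or signed.

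**Rolling windows, a conditional illustration.** If the 3-month visit rule is applied at monthly steps, adjacent points share two of three months. Treating points as three-month moving averages gives a lag-1 correlation of 2/3 and a lag-2 correlation of 1/3. In 20,000 simulated null series with 12 + 12 months, ordinary least squares rejects at the nominal 5% level in about 26% of series for level and about 30% for slope. The article states neither this window nor this estimator for the time series.

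**The case against.** The strongest reply is that the single baseline belongs to the descriptive comparison. Table 2 lists the time series separately, with its own monthly collection, and the network's feed is routine and does not depend on trial launch. Earlier months may therefore exist and may be intended. The wording about the study period describes the change to be estimated, not the first month of the series. This stands. A reader might infer that the series has only one pre-intervention point, or that monthly collection adds only post-launch points, but the article says neither.

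It is equally fair that the two denominators are tied to the baseline and the 3- and 6-month measures, not expressly to the monthly series. If the comparator clinics are measured in the same way, a definitional step also cancels in the controlled contrast, to the extent that it is equal in both groups.

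A reader might also take the 26% and 30% rejection rates as a defect of the plan, or conclude that no effect can be estimated. Neither follows. The rates assume a window, an estimator and 12 pre-launch months that the article does not state, and a controlled before-after contrast remains estimable with one pre-point.

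Finally, model form and handling of autocorrelation are properly left to a fuller plan. What does not fall away is that the schedules disagree (9 months in the abstract but not in Table 1; monthly in Table 2), none commits to a pre-launch series, and the only denominators given change exactly at launch.

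**Conclusion.** The point holds conditionally. If the monthly series begins at baseline, the pre-intervention slope and the level change at the first post-launch month cannot be separated (rank 3 of 4; 6 of 8 with comparators). If it begins earlier the model can be fitted, with useful precision from about 12 months under independent errors. The article does not settle which case applies. Separately, a step at launch would be partly definitional, by an unknown amount, if the stated baseline and follow-up measures enter the series.

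This is worth correcting before the data-sharing agreement is made. It is not a fatal flaw: the study is a five-practice feasibility trial with largely descriptive quantitative analysis, and the missing months may already be held.

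**What to change.** 1. In the data-sharing agreement, request monthly extracts for about 12 or more months before launch, if held, for the enrolled and comparator clinics. State the first month of the series.
2. Use the follow-up denominator both before and after launch.
3. Reconcile the abstract, Table 1 and Table 2 on the extraction schedule, including the 9-month point, and say which extractions feed which analysis.
4. If a rolling 3-month visit window is used at monthly steps, allow for the autocorrelation it induces or use non-overlapping windows.
5. If pre-launch months cannot be obtained, report a controlled before-after (difference-in-differences) comparison on one denominator and drop the time-series label. State that it assumes parallel trends, which a single pre-point cannot check.

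The cost is a slightly larger data request and a little more analysis work. No new data collection at the practices is expected, because the network already receives these records.

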#### Qualitative analysis

Audio files of interviews will be de-identified and professionally transcribed. Analyses will be conducted using NVivo (version 10 or higher).

Although the interview guides will be based on CFIR, inductive thematic coding will be used to ensure the findings are grounded in the data and not a pre-existing framework.

Summarised findings and early interpretations will be discussed with the research team in regular small team meetings. The authors will also meet on a minimum of two occasions with the entire investigator team to finalise the themes from the data.

Table 2 outlines the approach to the mixed-methods analysis of the data.

**Table 2. table2:** Mixed-methods data collection, analysis, and outcomes: implementation matrix adapted from Guetterman *et al*
^19^

**Data type**	**Study aim**	**Data collection procedure**	**Data analysis** **procedure**	**Theoretical framework**	**Products or outcomes**	**Points of integration**
Qualitative	To identify the barriers and facilitators to implementing alcohol BIs in general practice	Interviews: patients; clinicians; practice staff; PHN staff	Inductive thematic coding	CFIRRE-AIM	Perception of implementation processes from multiple viewpoints (acceptability; adoption; fidelity)	Triangulate with NoMAD data to inform implementation process.Compare with practice level data on % alcohol intake recording to look for patterns on increased uptake, or not
Quantitative	Increase uptake of alcohol BIs	Routine data extraction from practice to PHN (drinker, non-drinker, not recorded; sex; age); PHN to share the amalgamated data with research team	Descriptive statistics every 3 months.Interrupted time-series analysis compared with all practices in PHN catchment. Data will be collected monthly	CFIRRE-AIM	% change in patient records with alcohol intake recorded (reach; adoption)	Compare with qualitative interview data to understand barriers and facilitators to % change
Quantitative	To identify the barriers and facilitators to implementing alcohol BIs in general practice	NoMAD survey from practice managers and clinicians	Likert scale	Normalisation Process Theory	Measure of provider assessment of potential 'normalisation' of new procedure (acceptability; adoption; sustainability)	Triangulate with interview data from providers to identify implementation processes
Quantitative	Nested SMS study to determine response rates to SMS surveys over 9–12 months	SMS survey to patients at 3-monthly intervals using 2-way SMS (Qualtrics)	% response rate% of questions completed at each time point	NA	Response rate to SMS surveys over time	NA

BI = brief intervention. CFIR = Consolidated Framework for Implementation Research. NA = not applicable. NoMAD = Normalisation Measure Development. PHN = primary health network. RE-AIM = Reach, Effectiveness, Adoption, Implementation, Maintenance. SMS = short message service.

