## Method

This is a single-arm implementation trial using mixed methods to evaluate the uptake of ABIs in primary care. The approach is informed by: 1) the CFIR to assess factors affecting implementation and effectiveness; and 2) NPT to understand how change is embedded in a practice.

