### Study setting

The trial will be conducted in five general practice clinics located in northern metropolitan Melbourne, Australia, in a region corresponding to a primary health network (PHN) catchment (PHNs are federally funded to oversee primary care delivery in local regions).^12^

Participating general practice clinics will be located in a low-income area as identified by the PHN; that is, a Socio-Economic Indexes for Areas (SEIFA) score <1000, where a score of 1000 is the mean for all areas, and scores lower than this indicate relative disadvantage. Practices will use electronic patient medical record and billing software compatible with the PHN’s practice data extraction tool (Pen CS CAT4).^13^ Consent will be gained from practice management and at least one GP. No specific eligibility criteria will apply to participating GPs. No clinician in the practice will be mandated to use the resources. Patient participants will be aged >18 years and able to understand eighth-grade English. Interpreters will be used for patient interviews when necessary.

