### Recruitment

#### Practices

The PHN will recruit practices via newsletters and the PHN website. A member of the research team will then contact practice management to explain the project and seek written informed consent.

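### The trial clinics must be in low-income areas, but their time series is compared with the whole catchment, so area-specific change after launch could be read as an intervention effect

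*Protocol article*

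**What the plan says.** The design has no control arm: "This is a single-arm implementation trial using mixed methods to evaluate the uptake of ABIs in primary care" (Method). The Study setting section restricts the trial clinics by area: "Participating general practice clinics will be located in a low-income area as identified by the PHN", defined there as a SEIFA score below 1000. Clinics volunteer after PHN publicity: "The PHN will recruit practices via newsletters and the PHN website" (Recruitment, Practices).

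The comparator is described in three places, none with an area limit:

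- Quantitative instruments: "These measures will be available for all other clinics (approximately 850) in the same catchment area for comparison".
- Interrupted time series: the analysis covers the trial practices "as well as the 850 clinics within the same catchment to determine how much alcohol screening has changed in the intervention clinics and across whole", where the last words refer to the PHN.
- Table 2: "Interrupted time-series analysis compared with all practices in PHN catchment", with monthly data.

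The article mentions no restriction, weighting or adjustment of the comparator by area disadvantage. The low-income subgroup analysis under Quantitative instruments uses patients' self-reported status in the surveys, not the location of clinics. The Data analysis section lists relative effectiveness among the things to be assessed, and the Discussion expects evidence on the effectiveness of the strategy.

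**The concern.** The primary outcome is the change in the proportion of adult patients with a completed alcohol history. In a single-arm study, a concurrent series helps to separate the effect of the strategy from whatever else changed in that year. It does so only if the comparison clinics would have moved as the trial clinics would have moved without the strategy.

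Here the trial clinics are selected on area disadvantage and the comparison clinics are not. The Intervention section reports that the strategy was adapted for telehealth because of the pandemic, and the Discussion says that the pandemic may alter the findings. If the pandemic or the move to telehealth affected alcohol recording differently in poorer and better-off areas after launch, the gap between the two series would include that difference. It would look like an effect of the strategy, or hide one. This is more than a detail left to a fuller document, because the article names its comparator three times and each time names the unrestricted one.

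**Working it through.** The article gives no effect size, power or precision for the clinic-level comparison, so there is no stated figure to reproduce. Three checks follow.

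**1. Do the trial clinics sit inside their own comparator?** Quantitative instruments excludes them (all *other* clinics). Table 2, and the reference to the whole PHN under Interrupted time series, include them if read literally. Inputs: 5 trial clinics (Study setting) and about 850 others (Quantitative instruments). Share = 5 / (850 + 5) = 0.58%. With equal clinic weights, a true 10-point effect would read as 10 × (1 − 5/855) = 9.94 points. This is a wording conflict with no practical effect on the result.

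**2. What does an area-specific change do to a plain comparison of 12-month changes?** Two inputs are assumptions, because the article gives neither:

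- d: by how many percentage points a month the recording proportion in low-income clinics rises faster than in other clinics (0.1 to 0.5);
- s: the share of comparator clinics that are in low-income areas (0.2 to 0.8; s = 1 is the restricted comparator).

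With equal clinic weights the comparator moves by s × d a month relative to the better-off clinics, and the trial clinics by d. With no intervention effect, the apparent effect at 12 months is 12 × d × (1 − s):

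| d (points/month) | s = 0.2 | s = 0.5 | s = 0.8 | s = 1.0 |
|---|---|---|---|---|
| 0.10 | 0.96 | 0.60 | 0.24 | 0 |
| 0.25 | 2.40 | 1.50 | 0.60 | 0 |
| 0.50 | 4.80 | 3.00 | 1.20 | 0 |

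For example, 12 × 0.25 × (1 − 0.5) = 1.5 points. A negative d reverses the sign.

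**3. Does the interrupted time series remove it?** A noise-free two-group segmented regression was fitted to monthly points from 12 months before to 12 months after launch (assumed, since the article does not state the pre-launch length). Each group had its own pre-launch slope. The effect at month 12 is the difference in level change plus 12 × the difference in slope change.

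- If the areas diverge steadily throughout, the pre-launch slopes absorb it and the bias is 0.0 in every cell.
- If the divergence starts at launch, the bias equals the table above in every cell, so 1.5 points in the middle scenario.

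The exposure is therefore to change that differs by area from launch onward, and not to trend differences in general.

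**The case against.** The strongest reply is that the named method is an interrupted time series, whose first safeguard is each series' own earlier trend. The third check confirms this for steady divergence. A reader might infer that the catchment series is the only protection against secular change, or that any long-standing difference between poor and better-off areas would bias the result. The named method does not support either reading, provided that the model has group-specific slopes and enough earlier months. The article states neither, but an article may leave both to fuller documents.

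A reader might also infer that the authors expect recording trends to differ by area. They do not say so. The Background describes greater alcohol harm in low-income communities, and the Discussion says that the pandemic may alter findings. Neither speaks of differing trends in clinicians' recording. The share of the roughly 850 clinics below SEIFA 1000 is not given either, and if most qualify, the restriction changes little.

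Finally, the Interrupted time series section can be read as reporting two changes side by side, and for describing the whole PHN the whole catchment is the right series. That justifies keeping it as description. It does not justify using it as the main comparator while the article also intends to speak of effectiveness. The study is a feasibility trial, which limits the weight of the point but does not remove it.

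**Conclusion.** The point holds in a limited form. The trial clinics are restricted to low-income areas and the comparator is not, in all three places where it is described. Steady differences in trend can be handled by the model. Change that differs by area at or after launch cannot, and would be read as an effect of the strategy.

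The size and direction cannot be derived from the documents. The range of 0.24 to 4.8 points at 12 months rests on assumed values of d and s and only shows what such a divergence would do. It is not an estimate of the bias in this trial. It would be going too far to conclude that the comparison is biased by a known amount, or that including the trial clinics among the comparators matters, since that effect is about 0.6%. The feasibility aims are unaffected. The effectiveness statement would rest on firmer ground with a comparator chosen by the same area rule.

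**What to change.** Before extraction, ask the PHN for a monthly series from non-trial clinics that meet the same SEIFA rule, and name it as the main comparator. Keep the whole catchment as a secondary, descriptive series. Align Table 2 and the Interrupted time series section with the Quantitative instruments section, so that the trial clinics are excluded throughout. Acknowledge that the trial clinics are volunteers, a difference that the restriction does not remove.

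I would not also match on the pre-launch recording proportion, because clinics picked for an unusual level tend to drift back towards their own mean, and that drift would enter the comparison.

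The cost is modest. The PHN receives the data from all practices in the catchment and identifies the low-income areas, so it can apply the rule. Table 2 says that it will share amalgamated data. If that means one pooled series, a separate extraction is needed and the restriction cannot be made afterwards, hence the timing. There will be fewer comparator clinics. Their number is not stated, so the loss of precision cannot be calculated, although with only five trial clinics most of the uncertainty is likely to come from those five.
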